### Aim and hypotheses

The main aim of this project is to conduct a Randomized Controlled Trial (RCT) to evaluate a recently developed home-based alcohol prevention program, entitled "In control: No alcohol!" The program focuses on alcohol-specific parenting as a tool in delaying the age of alcohol onset in children. Onset of alcohol use is defined as the intake of the first glass of alcohol. With this RCT, including an experimental and a control group, we test whether fewer children have their first drink at an earlier age when included in the program. The second aim is to determine whether the program increases maternal use of several alcohol-specific parenting practices according to mothers and their offspring. The third aim is to test whether the prevention program differs between families varying on parental own drinking.

More specifically, we expect that a) a significant lower percentage of children who followed the program will have had their first glass of alcohol at the last follow-up compared to children who did not follow the program. b) mothers who followed the program are significantly more likely to engage in alcohol-specific parenting than mothers who did not follow the program. We expect that mothers involved in the program (as compared to controls) will set and keep stricter rules about alcohol, are more involved in constructive communication on alcohol-related topics, have more confidence in discussing alcohol matters, reduce children's access to alcohol beverages, make a rule with their children about not drinking before a certain age and are more likely to monitor children's activities. c) Above average drinking mothers that follow the program are more likely to increase their alcohol-specific parenting as compared to below average drinking mothers that follow the program.

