### Sample Size Calculation

Based on the outcomes of parent-adolescent interventions in the Netherlands and the United States [14,21], we expect a minimal 10% difference in initiation rates between the control and experimental group at the third follow up, which is approximately 12 months after the end of the prevention. Equal cell sizes are assumed for study cells and power of .80 has been targeted. The primary hypothesis, a significant lower percentage of children who have their first glass of alcohol in the prevention group than in the control group, will be tested at an overall significance level of 0.05 (two-sided). G-Power was used to calculate the estimated sample sizes for two-sample comparison of proportions. Based on the prevalence of alcohol use in 13 year olds (age of the children at 18 months follow-up), which is 55%, we need 404 children per condition. However, if we take into account possible attrition (0.80), the fact that data are clustered (mother-child dyads are nested within schools) and the fact that we apply multiple imputation in the case of missing data (factor 1.4), we end up with 656 children per condition ((183/0.80) * 1.4)). Thus, 1312 mothers (and children) are required to participate. In accordance with the intention-to-treat philosophy, all children randomized to one of the conditions are included in analyses to test the study hypotheses.

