#### Outcomes

The primary outcome, initiation of alcohol use, is defined as have been drinking at least one glass of alcohol. Secondary outcome measures are alcohol-specific parenting dimensions such as rules about alcohol, non-drinking agreement, alcohol availability at home, and frequency and quality of alcohol-specific communication (e.g., [7,26]), but also general parental monitoring [27] and parent-child relationship quality [28]. Other outcomes are susceptibility to drinking alcohol, defined as the lack of a firm commitment against drinking alcohol [29,30], alcohol expectancies [31], self-efficacy [32,33], and frequency and intensity of child alcohol use [34]. The Strengths and Difficulties Questionnaire (SDQ) [35] will be used as a behavioral screening instrument for early detection of psychological problems. Psychological problems are associated with problem behaviors like drinking alcohol at an early age (e.g., [36]).

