#### Statistical analyses

In accordance with the intent-to-treat philosophy, all children randomized to a condition will be included in the analyses to test the study hypotheses. Moreover, while randomization takes place on school level and children are 'nested' within these schools, we need to control for clustered data [37]. Mplus is a statistical modeling program that has special features to deal with missing data and it allows analyses with complex data while taking into consideration the longitudinal character of the data and the fact that data are clustered. Regression analyses for dichotomous outcome measures (logistic regression) will be conducted to test whether children in the control condition are more likely to initiate drinking than children in the experimental condition [14,37]. For the second aim of our study, namely, that mothers in the prevention group will use more alcohol-specific socialization strategies than mothers of the control group, we will perform mediation analyses in Mplus, using the bootstrap method [37]. To test our third hypothesis of the study, possible moderating effects of relevant demographic indices such as gender, as well as mothers' alcohol use at baseline, we will create products of the predictors and then include those interaction terms in the logistic regression model (e.g., condition * mothers' drinking; [37]).

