### Strengths and limitations

An important strength of the program "In control: No alcohol!" is that it is theory driven. The underlying structure of the program is based on the Social Cognitive Learning Theory [4], and the Elaboration Likelihood Model [25], while the content is based on recent alcohol-specific parenting research [7-10,26]. Second, the program reaches children during the pre-initiation stage of alcohol use, aiming to prevent them from drinking their first alcoholic beverage, and thereby lowering the odds of heavy drinking [2,3]. Third, parents can complete the program with their children at home at a time of their choice. This creates the opportunity to include parents in the study, who are normally more difficult to reach for alcohol prevention, like parents who drink alcohol.

A strength of the study design is that it also includes long-term follow-ups at 12 and 18 months, in addition to the immediate follow-up at 6 months. This will create more opportunity to find an effect on actual alcohol use of the children, as well as mediating effects through alcohol-specific parenting practices. Further, if the "In control: No alcohol!" program turns out to be effective, it can easily be implemented on a large scale via primary schools. A limitation of the study is that only mothers can participate. While there are several good reasons for this choice (e.g. mothers are more likely to spend time with their children and to enroll in health-related programs), previous research has shown differences in alcohol-specific socialization between mothers and fathers; For example, mothers communicate more often about alcohol [7,38] and are more understanding towards their children [39] compared to fathers. In future research, the effect of the program, when targeted at fathers, should be investigated.

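### The second aim is assigned to bootstrapped mediation, and the condition-to-parenting effect that would test hypothesis (b) is not named as its test

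*Protocol article*

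**What the plan says.** The protocol article sets the aim in Aim and hypotheses: "The second aim is to determine whether the program increases maternal use of several alcohol-specific parenting practices according to mothers and their offspring". Hypothesis (b), in the same section, expects that "mothers who followed the program are significantly more likely to engage in alcohol-specific parenting than mothers who did not follow the program". It then lists rules, constructive communication, confidence, access to alcohol, an agreement on not drinking before a certain age, and monitoring. The child's drinking is not part of (b).

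The Outcomes section gives these measures a standing of their own: "Secondary outcome measures are alcohol-specific parenting dimensions such as rules about alcohol, non-drinking agreement, alcohol availability at home", followed by communication, monitoring and relationship quality.

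The Statistical analyses section restates the second aim, again as a contrast between arms: "that mothers in the prevention group will use more alcohol-specific socialization strategies than mothers of the control group". The same sentence then gives the method: "we will perform mediation analyses in Mplus, using the bootstrap method". No other analysis is named for this aim. The one main-effect regression that is named is logistic and serves the primary outcome, "to test whether children in the control condition are more likely to initiate drinking than children in the experimental condition".

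**The concern.** The hypothesis and the method named for it have different targets. Hypothesis (b) asks whether allocation changes parenting. A bootstrapped mediation analysis is ordinarily run to get an interval for the effect of allocation on drinking that passes through parenting. That effect is non-zero only if allocation changes parenting and parenting in turn changes drinking.

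Two things are at stake. First, if the programme changes parenting but a given parenting dimension has little bearing on drinking within 18 months, the indirect effect is null while (b) is true. Second, randomisation protects the comparison of arms on parenting, but it does not protect the parenting-to-drinking link. Families that set stricter rules may differ in other ways that affect whether a child drinks. Judging (b) by the indirect effect would make a question that randomisation can answer depend on one that it cannot.

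**Working it through.** **Step 1: set the texts side by side.** Let a be the effect of condition on parenting and b the effect of parenting on drinking, given condition.

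- Hypothesis (b), and the second aim as restated in Statistical analyses, concern a alone.
- The indirect effect is a × b.
- Strengths and limitations uses mediation in this ordinary sense. Beside a possible effect on the children's actual alcohol use, it says the later follow-ups give more opportunity to find effects, "as well as mediating effects through alcohol-specific parenting practices".

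So the article's own use of the word points to a × b, and its hypothesis points to a.

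**Step 2: the logic.** If b = 0, then a × b = 0 for any a. A null result for a × b is therefore compatible with (b) being true.

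**Step 3: an illustration of size.** The article states no power or effect size for any parenting outcome, so all effect sizes here are assumed.

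- Analysed number: 656 per arm, taken back through the article's own factors, is 656 / 1.4 × 0.80 = 374.9, so about 375 per arm.
- Parenting and drinking are treated as continuous with unit residual SD, without clustering. Each setting has 400 replicates.
- Direct test: two-sided 5% z-test of a.
- Indirect test: 95% percentile-bootstrap interval for a × b, 300 resamples.

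| a (SD) | b | direct test rejects | indirect effect rejects |
|---|---|---|---|
| 0.3 | 0 | 99.0% | 5.5% |
| 0.3 | 0.1 | 98.75% | 77.0% |
| 0.3 | 0.3 | 98.0% | 98.25% |
| 0 | 0.3 | 5.5% | 6.25% |

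The simulation error is small against these contrasts: √(0.77 × 0.23 / 400) = 0.021 at 77%, and √(0.055 × 0.945 / 400) = 0.011 at 5.5%.

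**Step 4: a check by formula.**

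- Direct test: SE of a = √(2/375) = 0.0730; 0.3 / 0.0730 = 4.11; power = Φ(4.11 − 1.96) = Φ(2.15) = 0.984. This does not involve b, so the spread from 98.0% to 99.0% in the table is simulation noise.
- Link at b = 0.1: SE of b ≈ 1/√750 = 0.0365; 0.1 / 0.0365 = 2.74; power = Φ(2.74 − 1.96) = Φ(0.78) = 0.782.
- Both paths significant: 0.984 × 0.782 = 0.77, as simulated.
- At b = 0 the same product is 0.984 × 0.05 = 0.049, within simulation error of 5.5%.

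The two tests agree when b is strong and part completely when b is zero.

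**The case against.** The strongest reply is that a mediation model with condition as predictor and parenting as mediator must estimate the condition-to-parenting path. That path is the randomised comparison of arms on parenting and needs no assumption about drinking. The sentence opens with the contrast in (b), so the authors may well have meant that path as the test. The same section also says that clustering by school must be controlled for. All of this stands. A reader might infer that the plan contains no comparison of the arms on parenting, or that the second aim would be declared negative whenever the indirect effect is null. The text supports neither. The comparison sits inside the model, and no sentence says that the indirect effect decides (b). What remains is that no sentence says the path decides it either, and bootstrapping is ordinarily aimed at the product.

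It is also fair to say that mediation is a declared interest. Aim and hypotheses presents parenting as the means by which onset is to be delayed, and Strengths and limitations mentions mediating effects. Two related analyses were probably merged into one sentence. That explains the wording but does not supply the missing test, since none of the lettered hypotheses asks a mediation question.

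A condensed article may leave model details to an analysis plan. Here, however, the method is not left open: one is named, and it does not match the hypothesis.

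Finally, no fixed loss of power can be read from the document. A reader might multiply 0.80 for the first path by 0.50 to 0.80 for the second and quote 0.40 to 0.64. Those path powers are assumptions. The 0.80 in Sample Size Calculation belongs to child initiation, as does the 0.05 level.

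**Conclusion.** The point holds in a limited form. The only analysis named for hypothesis (b) is one whose usual target, the indirect effect, is not (b). The parameter that would test (b) is in the model but is not designated as the test. A null indirect effect would not refute (b), and the indirect effect rests on a link that was not randomised.

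The size cannot be fixed from the document. Under the assumptions above (375 per arm, a = 0.3 SD, continuous variables, no clustering), the loss of power runs from negligible with a strong parenting-to-drinking link to near total with none. The trial has a binary drinking outcome and school clusters, so the percentages illustrate the direction and range and do not predict this trial's power. The qualitative conclusion does not depend on them.

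This should be fixed. It concerns a secondary aim. The primary hypothesis, its logistic regression, the randomisation and the sample size are unaffected.

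**What to change.** State in Statistical analyses that hypothesis (b) is tested by the effect of allocated condition on each parenting outcome. Use a regression suited to the scale of the outcome (linear, ordinal or logistic), account for clustering by school, and adjust for the baseline value of the same measure where it is collected.

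Table 1 shows monitoring, availability of alcohol at home, rules and communication at every wave. It has no separate row for maternal confidence or for the non-drinking agreement. They may sit within other rows, so the sponsor should confirm that both are measured at baseline.

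State mediation separately as an explanatory analysis, with the mediator measured before the drinking outcome. The waves allow parenting at 6 or 12 months and drinking at 18 months.

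The cost is a few sentences and a few added regressions. No new data are needed for the four measures in Table 1; for the other two this depends on the confirmation above.

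### The third hypothesis is about mothers' parenting, but its interaction test sits in the logistic model for child initiation, so no analysis described in the article tests it

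*Protocol article*

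**What the plan says.** Under Aim and hypotheses, the third aim is broad and names no outcome: "The third aim is to test whether the prevention program differs between families varying on parental own drinking". Hypothesis (c), which makes that aim specific, does name one: "Above average drinking mothers that follow the program are more likely to increase their alcohol-specific parenting as compared to below average drinking mothers". Its outcome is the mother's alcohol-specific parenting and its moderator is her own drinking.

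The Statistical analyses section then describes three analyses:

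- For the primary hypothesis, a logistic regression with the child's initiation as outcome: "logistic regression) will be conducted to test whether children in the control condition are more likely to initiate drinking".
- For the second aim, on parenting: "we will perform mediation analyses in Mplus, using the bootstrap method". No moderator is mentioned.
- For the third hypothesis, the text opens with "To test our third hypothesis of the study, possible moderating effects of relevant demographic indices such as gender, as well as mothers' alcohol use" and continues that "we will create products of the predictors and then include those interaction terms in the logistic regression model". The example given is the product of condition and mothers' drinking.

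The Outcomes section keeps the two kinds of outcome apart: initiation is primary, and the parenting dimensions are secondary.

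**The concern.** The hypothesis and the model named to test it have different dependent variables. The hypothesis asks whether the program changes what heavier-drinking mothers do more than it changes what lighter-drinking mothers do. The planned term asks whether the program's effect on the child's first drink differs between those families.

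The risk lies in interpretation. A null interaction on initiation could be reported as refuting (c), and a positive one as confirming it, when neither speaks to parenting. If a parenting model were chosen only after the data were seen, there would be room for selection. Table 1 has four parenting rows (monitoring, availability at home, rules, communication), each reported by mother and child at three follow-ups, which gives 4 × 2 × 3 = 24 combinations before any sub-dimension is counted.

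**Working it through.** The article prints no figure on this point, so the check sets the texts side by side.

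| Element | Hypothesis (c), Aim and hypotheses | Test named for the third hypothesis, Statistical analyses |
|---|---|---|
| Dependent variable | Mother's alcohol-specific parenting (secondary outcome) | Child's initiation (primary outcome), the only outcome given to a logistic model |
| Moderator | Mother's drinking, above or below average | Mother's drinking at baseline; also demographic factors such as gender |
| Arms used | Worded within the program arm | Both arms, through a product with condition |

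**Step 1: which model is meant.** The article refers to the logistic regression model with a definite article, and it has described one such model, for initiation. That is the natural antecedent.

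**Step 2: what each model estimates.** Write C for condition, D for mother's baseline drinking, Y for initiation, and P for a parenting measure.

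- Planned: logit Pr(Y = 1) = b0 + b1·C + b2·D + b3·C·D.
- Needed for (c): P at follow-up = g0 + g1·C + g2·D + g3·C·D + g4·P at baseline, with school clustering and a link suited to the measure.

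Hypothesis (c) is a statement about g3. The plan estimates b3.

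**Step 3: whether b3 can stand in for g3.** On the program's own theory, the effect on initiation in a drinking stratum d is made up of the effect on parenting (a_d), carried through the effect of parenting on initiation (m_d), plus any direct effect (c_d). Hypothesis (c) compares a_d between strata. The initiation interaction compares the combined result. If m_d or c_d differs between strata, b3 can be null while the a_d differ, or non-null while the a_d are equal. Neither result for b3 settles g3.

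**Step 4: whether another described analysis supplies g3.** The bootstrap mediation contains a path from condition to parenting, which serves hypothesis (b). It is described without a drinking interaction, so it gives one path for all mothers and no contrast between strata.

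**Step 5: whether parenting is really the intended outcome of (c).** The Background reports a pilot finding of the same shape: among mothers drinking more than average, the program improved the quality of communication about alcohol. That is a parenting result, and (c) parallels it.

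**Step 6: whether the data allow the right test.** Table 1 lists parental alcohol use, rules, availability, communication and monitoring at baseline and all three follow-ups, from mother and child.

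**The case against.** **The third aim is broad enough to cover the planned test.** This stands in part. An interaction on initiation does answer one reading of that aim, and it is not an invalid analysis. But the article says that it tests the third hypothesis, and (c) is explicitly about parenting.

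**Some parenting measures may be binary.** The sentence "Regression analyses for dichotomous outcome measures (logistic regression) will be conducted" speaks of outcome measures in the plural, and a non-drinking agreement could be modelled by logistic regression. This softens the point without answering it. The sentence goes on to name initiation only, and rules, communication and monitoring would not obviously fit such a model.

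**An article condenses, and a fuller plan may exist.** This limits the claim to the analyses described here. It does not remove it, because the article does not leave the model open: it names one, and that model has a different outcome.

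A reader might also infer more than the documents support:

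- *That a comparison within the program arm is planned.* Only the wording of (c) suggests this. The analysis section specifies a product with condition, which needs both arms.
- *That regression to the mean would produce a spurious larger increase.* The groups are formed on drinking, not on extreme parenting scores. The Background says that drinking parents tend to engage less in these practices. That is a difference in starting level, and it calls for baseline adjustment.
- *That the interaction is underpowered and that this is part of the defect.* The article powers only the primary hypothesis and gives no split of mothers by drinking. Power for the initiation interaction also says nothing about a test on parenting.

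**Conclusion.** The point holds as a mismatch between hypothesis and model. Hypothesis (c) concerns the program's effect on parenting according to mothers' drinking, the model named for it has child initiation as its outcome, and no other described analysis combines a parenting outcome with a drinking interaction.

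Its extent is one of three stated hypotheses, on secondary outcomes. The primary hypothesis, randomization, sample size and data collection are untouched, so it should be fixed but does not threaten the trial's main result. There is no numerical size to attach.

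The conclusion rests on reading the logistic regression model as the only one the article describes, and on the article alone, since an unseen analysis plan may add a suitable test.

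**What to change.** 1. In Statistical analyses, test (c) with a condition by baseline maternal drinking term in models whose dependent variables are the parenting outcomes. Use both arms, include the baseline value of the same parenting measure as a covariate, and account for school clustering. State in advance which parenting dimension, reporter and follow-up carry the test.
2. Reword (c) as a difference in the program-versus-control effect on parenting between mothers who drink above average and those who drink below average.
3. Keep the interaction on child initiation, and report it as a separate moderation question under the broad third aim, not as the test of (c).

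The cost is a few sentences of text and some added models. Table 1 already provides maternal drinking and the main parenting measures at every assessment, so recruitment, questionnaires and sample size do not change.
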